## Abstract

**Introduction:**

Palliative and end-of-life care in care homes is often inadequate, despite high morbidity and mortality. Residents can experience uncontrolled symptoms, poor quality deaths and avoidable hospitalisations. Care home staff can feel unsupported to look after residents at the end of life. Approaches for improving end-of-life care are often education-focused, do not triage residents and rarely integrate clinical care. This study will adapt an evidence-based approach from Australia for the UK context called ‘Palliative Care Needs Rounds’ (Needs Rounds). Needs Rounds combine triaging, anticipatory person-centred planning, case-based education and case-conferencing; the Australian studies found that Needs Rounds reduce length of stay in hospital, and improve dying in preferred place of care, and symptoms at the end of life.

**Methods and analysis:**

This implementation science study will codesign and implement a scalable UK model of Needs Rounds. The Integrated Promoting Action on Research Implementation in Health Services (i-PARIHS) framework will be used to identify contextual barriers and use facilitation to enable successful implementation. Six palliative care teams, working with 4–6 care homes each, will engage in two phases. In phase 1 (February 2021), stakeholder interviews (n=40) will be used to develop a programme theory to meet the primary outcome of identifying what works, for whom in what circumstances for UK Needs Rounds. Subsequently a workshop to codesign UK Needs Rounds will be run. Phase 2 (July 2021) will implement the UK model for a year. Prospective data collection will focus on secondary outcomes regarding hospitalisations, residents’ quality of death and care home staff capability of adopting a palliative approach.

**Ethics and dissemination:**

Frenchay Research Ethics Committee (287447) approved the study. Findings will be disseminated to policy-makers, care home/palliative care practitioners, residents/relatives and academic audiences. An implementation package will be developed for practitioners to provide the tools and resources required to adopt UK Needs Rounds.

**Registration details:**

Registration details: ISRCTN15863801.

Strengths and limitations of this studyUsing implementation science will improve the chances of Needs Rounds being successfully implemented across the sites.Data collection techniques will flexibly use video interviews and virtual workshops to accommodate lockdown and social distancing measures.Care home staff collection of resident data will prevent the need for research staff to access personal data or enter care homes when there are concerns about COVID-19 transmission.

## Introduction

Care home residents (hereafter referred to as residents) are an ageing population and are often frail with multiple complex health needs.^1 2^ Older people’s care homes in the UK experience high mortality rates, with between 26%^3^ and 56%^1^ of care home residents dying in the first year of admission. Care homes, including those with and without registered nurses (RNs), increasingly look after older people with complex multiple morbidities.^4^ Projections show that if current trends continue, care homes will be the most common place of death by 2040.^5^

Residents often experience inadequate end-of-life care as a result of avoidable hospitalisations,^6^ unmanaged symptoms, poor anticipatory/advance care planning^7^ and communication barriers.^8 9^ Staff report difficulties with interdisciplinary working,^10^ and low confidence and capability^7^ in managing symptoms and identifying when people are dying, deficiencies exacerbated by workforce issues, including staff shortages, high turnover^11 12^ and time restrictions.^13^

Residents often have multiple admissions to hospital prior to their death,^6^ with some admissions potentially preventable.^14^ Hospitalisations are costly and may prompt futile interventions that can cause distress to residents and family members.^15^ Developing evidence-based approaches to support older people at the end of life, and reducing avoidable and often detrimental admissions to acute care, must therefore be a priority.

A systematic review of end-of-life care in UK care homes calls for the extension of specialist palliative care in care homes.^10^ Key issues reported include staff struggling to identify when residents are approaching end of life and unanticipated deterioration impacting decision-making about hospitalisations. Anticipatory/advance care planning training needs were also highlighted, with staff frequently avoiding these conversations due to lacking confidence and knowledge. The need to strengthen interdisciplinary working to address reactive decision-making and improve understanding about who is responsible for discussions about end-of-life care was also described.

Providing end of life support to care homes is a growing area of service development. Current approaches such as ECHO (Extension of Community Healthcare Outcomes),^16^ Gold Standard Framework (GSF),^17^ Macmillan’s education for carers ‘Foundations in Palliative Care’, Six Steps to Success,^18^ PACE (Palliative Care Across Europe)^19^ and the Namaste programme^20^ offer staff training, yet rarely facilitate evidence-based clinical input for people diagnosed as dying. Both the GSF^21^ and PACE^22^ recommend monthly interdisciplinary meetings, although this is often variable in practice. Furthermore, such interventions often fail to change behaviour.^23 24^

This study aims to address recognised deficits in the provision of palliative and end-of-life care in care homes, by using an implementation science approach to alter practice and embed a promising approach developed in Australia called ‘Palliative Care Needs Rounds’ (Needs Rounds). Needs Rounds improve palliative and end-of-life care by reducing unnecessary hospitalisations, increasing staff knowledge and capability, improving anticipatory/advance care planning and strengthening interagency working.

### Intervention description

Needs Rounds are monthly hour-long triage meetings focused on 8–10 residents in each care home who are at risk of dying without a plan in place. A checklist^25^ is used to identify the most appropriate residents to discuss. Needs Rounds are chaired by a palliative care specialist and attended by care home staff who discuss each resident’s physiological, psychosocial and spiritual needs. This instigates a number of tailored actions, which are always personalised for the individual, including medication reviews, case conferences, anticipatory/advance care planning and referrals to relevant specialists.

Needs Rounds have a strong evidence base to support their uptake. Research in Australia demonstrated a number of positive outcomes. Needs Rounds reduced the length and number of hospitalisations,^26 27^ increased resident dying in their preferred place,^26^ with dignity, compassion and comfort,^28^ enabled staff to normalise death and dying,^29^ and improved workforce confidence.^28^

### Aims and objectives

This study aims to codesign and implement an appropriate scalable UK model of Needs Rounds, which offers specialist palliative care outreach to care homes, in order to improve the lives and deaths of residents. The objectives are:

### Implementation

Codesign a UK version of Needs Rounds, which is responsive to the different (macro, meso and micro) contextual characteristics of the UK care home sector.Implement the adapted model of care, assess feasibility, acceptability and effectiveness, and ultimately propose how the model of care can be further refined and adopted in the UK context, to reap the benefits demonstrated in the Australian work.

### Intervention

Determine the transferability of the core elements of the Needs Rounds intervention in a UK context.Delineate the mechanisms of action that enable more effective palliative and end-of-life care practices to be realised in UK care homes.Identify the relationships between (1) the mechanisms of action embedded in Needs Rounds, (2) how these mechanisms function in different care home contexts and (3) the outcomes arising for different stakeholders and parts of the care system.

### Process evaluation

Document the outcomes of UK Needs Rounds on hospitalisations (including costs), quality of death/dying and staff capability.Assess and report the perspectives of care home residents/relatives/staff and palliative care staff on using UK Needs Rounds.Map the UK Needs Rounds fit for services not engaged in the implementation study.Identify the outcomes, impact and experience of patient/public involvement (PPI) in the study.

## Methods and analysis

This pragmatic critical-realist implementation study^30^ will use the Integrated Promoting Action on Research Implementation in Health Services (i-PARIHS) framework^31 32^ in six case studies. Each case comprises a specialist palliative care team working with 4–6 care homes each.

i-PARIHS represents an integrated approach, recognising that most implementation is complex, requiring attention to multiple factors simultaneously for an innovation to be successful. The development of theory is central to i-PAHRIS and enables effective implementation of research evidence into everyday practice.^33^ Programme theories explaining micro changes and transactions, such as working hypotheses or local theories of change, are explored to elucidate core concepts. From these, mid-range theories are developed that have greater explanatory potential to predict and plan for change across different settings.^33^ For this study, theories will be generated regarding (1) influential components of the UK context and (2) the mechanisms of how to implement Needs Rounds in care homes in order to deliver desired outcomes.

Facilitation is also critical for successful implementation.^31^ Facilitators are agents of change who lead or champion an innovation. Facilitators for each case will be identified during phase 1 data collection.^34^ Recognising the likelihood of high turn-over of staff in care homes, at least two key staff members (facilitators) will be identified for each care home.

### Target sites and population

Four case study sites will be in England and two in Scotland. Each site consists of a palliative care specialist service which will work with 4–6 care homes in their local area. Recruitment will be undertaken by the hospices with support from the research team and ENRICH (a national network for care home research) where necessary.

Purposive maximum variability sampling of specialist palliative care services will focus on recruiting a heterogeneous and information-rich sample to reflect, for example: urban/rural, service size, deprivation, cultural demographics, use of ECHO^35^ or other specialist palliative care input models, hospital at home services and care home support teams, national charity/independent management, funding models, and hospital transfer policies. These variables reflect the dominant contextual influences which are likely to impact how Needs Rounds are used in the UK.

Table 1 provides a breakdown of the inclusion criteria for each participant group. The qualitative sample (n=40 interviewees) seeks adequate depth and breadth to determine the implementation objective: ‘what works for whom under what circumstances’. Interview sample sizes are based on the Australian studies, and are congruent with accepted standards for qualitative data interpretation.^36^

**Table 1 T1:** Sample and inclusion criteria

Participant	Inclusion criteria
Stakeholders (phases 1 and 2 interviews). n=40	Work for the specialist palliative care service or a care home (with or without registered nursing) in one of the six cases; or are a resident in one of the care homes; or are a relative of a care home resident in one of the six cases; or work in acute care impacted by hospitalised care home residents Willing to provide informed consent Have capacity to provide their own consent to participate Not engaged in any current safeguarding investigations.
Care homes (adopting Needs Rounds as their new standard of care). n=28–36	Located near to the specialist palliative care team Provide care to residents who have high clinical nursing/medical needs Willing to sign a memorandum of understanding with the research team, outlining resident demographics and health service use data, facilitate access to staff for interviews, and engagement in Needs Rounds A range of sizes (focusing primarily on larger care homes, following CQC data indicating lower quality in larger facilities),^46^ sole traders and large corporate provider, and with a range of funding models (NHS/social care and self-funded residents).
Residents (discussed at Needs Rounds in phase 2) Estimate of n=1500	Resident in a collaborating care home in one of the six case study locations An anticipated life-expectancy of less than 6 months At risk of dying without appropriate planning in place Experiencing inadequately managed bio-psychosocial symptoms Not engaged in any current safeguarding investigations Able to provide their own informed consent
Relatives (completing outcome measures in phase 2) n=300	The relative of a resident who was discussed in Needs Rounds Able to provide their own informed consent.
PPI evaluation n=15	Coinvestigator or a member of one of the case study sites Able to provide their own informed consent

CQC: Care Quality Commission; NHS: National Health Service

For the quantitative sample, the average size of the care homes is anticipated to be 52 beds, and the rate of emergency admission to hospital to be 0.173 per bed within the 4-month period,^37^ with an average of 9 admissions per care home. A sample of 30 care homes would allow change to be identified in the hospitalisation rate of 0.02 per bed (α=0.05, β=0.2, ΔSD=0.040). This is sufficient to detect a clinically meaningful change in the primary outcome (reduction of one hospitalisation per 4 month period in a typical care home) for the quantifiable data in phase 2.

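### Table 1's lower limit of 28 care homes does not follow from six teams with 4–6 homes each (24–36), and both lower limits fall below the 30 homes behind the power statement.

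*Protocol article*

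**What the plan says.** The number of teams and of homes per team is consistent wherever it appears. The Abstract has "Six palliative care teams, working with 4–6 care homes each, will engage in two phases". The opening of Methods and analysis has "Each case comprises a specialist palliative care team working with 4–6 care homes each". Target sites and population has "Each site consists of a palliative care specialist service which will work with 4–6 care homes in their local area", and it confirms six sites: "Four case study sites will be in England and two in Scotland".

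Table 1, in the same section, is the only place that gives a range for the total number of homes: "Care homes (adopting Needs Rounds as their new standard of care). n=28–36".

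The sample-size paragraph below Table 1 uses a third figure: "A sample of 30 care homes would allow change to be identified in the hospitalisation rate of 0.02 per bed", with the inputs "α=0.05, β=0.2, ΔSD=0.040". It concludes that this is enough to detect one fewer hospitalisation per four months in a typical home, which it takes to have 52 beds. The economic analysis section plans paired t-tests comparing the four months before implementation with months 9–12 of delivery.

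**The concern.** Table 1's upper limit, 36, is exactly six teams times six homes, so the range appears to come from that multiplication. The lower limit is not six times four. A total of 28 is 4.67 homes per team, and the article neither explains it nor sets a minimum total elsewhere.

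This matters because the SD of change in the power statement applies to homes, so the number of homes fixes the power of the paired comparison. A study with four homes at every team would meet the per-team range, miss the Table 1 range and be six homes (20%) short of the 30 assumed. A study at Table 1's own lower limit would be two homes (7%) short. The article does not say what power either would have. The hospitalisation estimate and its 95% CI also carry into the cost-effectiveness range and the five-year projections, so lost precision affects more than one test.

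**Working it through.** **Inputs, all from the protocol article**
- Six teams, 4–6 homes each (Abstract; Methods and analysis; Target sites and population).
- 28–36 homes (Table 1).
- 30 homes, change δ = 0.02 per bed, SD of change σ = 0.040, α = 0.05, β = 0.2, 52 beds per home (sample-size paragraph).
- Paired t-test (economic analysis section).
- Assumption: two-sided test, because sidedness is not stated.

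**Range of homes**

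6 × 4 = 24 and 6 × 6 = 36. Table 1's 28 equals 28/6 = 4.67 homes per team. The assumed 30 equals 30/6 = 5 homes per team.

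**Reproducing the plan's 30**

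Normal approximation for a paired difference: n = (σ(z₀.₉₇₅ + z₀.₈₀)/δ)² = (0.040 × (1.960 + 0.842)/0.02)² = 31.4, so 32 homes. At n = 30 the power is Φ(0.5√30 − 1.960) = Φ(0.779) = 78.2%. The change detectable with 80% power is 0.040 × 2.802/√30 = 0.0205, which rounds to 0.02. The plan's figure is therefore reproduced, within rounding, by the two-sided normal formula.

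**Power across the permitted range**

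Standardised change δ/σ = 0.02/0.040 = 0.5. Normal power is Φ(0.5√n − 1.960). Paired t power comes from the noncentral t distribution with n − 1 degrees of freedom and noncentrality 0.5√n.

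| Homes | Where it comes from | Normal, two-sided | Paired t, two-sided | Paired t, one-sided |
|---|---|---|---|---|
| 24 | 6 × 4 | 68.8% | 65.0% | 76.8% |
| 28 | Table 1 lower limit | 75.4% | 72.3% | 82.5% |
| 30 | power statement | 78.2% | 75.4% | 84.8% |
| 36 | 6 × 6; Table 1 upper limit | 85.1% | 83.1% | 90.3% |

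The two-sided paired t-test first reaches 80% at 34 homes (80.8%).

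**Change detectable with 80% power, two-sided paired t**
- 24 homes: 0.0239 per bed, × 52 = 1.24 admissions per home.
- 28 homes: 0.0220 per bed, 1.14 admissions.
- 30 homes: 0.0212 per bed, 1.10 admissions.
- 36 homes: 0.0192 per bed, 1.00 admission.

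The plan's target of 0.02 per bed is 0.02 × 52 = 1.04 admissions.

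**Separating the two sources of shortfall**

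At 30 homes, moving from the normal formula to the paired t-test costs 78.2 − 75.4 = 2.8 points, whatever the range of homes. Within the paired t column, going from 30 to 28 homes costs 75.4 − 72.3 = 3.1 points, and going from 30 to 24 costs 75.4 − 65.0 = 10.4 points.

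**The case against.** A reader might infer that the three figures cannot all be true. The documents do not support that. Five homes per team gives 30, which meets the per-team range, lies inside Table 1's range and equals the assumed sample. The whole of 28–36 lies within 24–36, and 28 is reachable with teams of 4, 4, 5, 5, 5 and 5. A per-team range and a narrower range for the total can coexist.

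It can also be argued that Table 1, as the only stated range for the total, rules out 24 homes. The shortfall is then two homes, or about three points of power. That is a fair reading, but the article does not say that Table 1 overrides the per-team range, and 28 is still below 30.

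A third objection is that setting 65% or 72% against a nominal 80% overstates the effect of the number of homes. This stands: the same paired t method gives only 75% at the plan's own 30 homes, so part of each gap comes from the method. Sidedness also matters. If the test were one-sided, 28 homes would give 82.5%, although 24 would still give only 77%.

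Finally, the Outcomes section makes the primary outcome qualitative and health service use secondary. That limits the weight of the point. It does not remove it, because the sample-size paragraph treats hospitalisation as primary among the quantifiable outcomes and the cost analysis depends on it.

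**Conclusion.** The point holds at the low end of the permitted range only. Table 1's lower limit of 28 is unexplained against the 24 implied by the design text, and both are below the 30 homes behind the power statement. Assuming a two-sided test and the plan's own change and SD, power at 24–28 homes is 69–75% by the normal approximation that reproduces the plan, or 65–72% by the planned paired t-test. Only the 24-home result is below 80% on every reading, including a one-sided test.

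It would be wrong to conclude from this that the study as a whole is underpowered, or that 24 homes is the intended sample. The figures agree at five homes per team, and 36 homes gives more than 80% by either method. The defect is an unreconciled minimum with no power attached to it, for an outcome that is secondary overall but is the powered quantitative one.

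**What to change.** State one range and one minimum total of homes, with Table 1 and the per-team range reconciled so that each follows from the other, or with the reason for a narrower total given. In the sample-size paragraph, say whether the test is one- or two-sided, and give the power or detectable change for the planned paired t-test at that minimum and at 30 homes. For example, if the minimum is 24 and the test is two-sided, the detectable change with 80% power is about 0.024 per bed, or 1.2 admissions per 52-bed home.

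Lowering Table 1 to 24, or raising the design text to 5–6 homes per team, would align the numbers but would not be enough alone. The first formally permits the weakest case, and the second sets a minimum of 30 homes, where the two-sided paired t-test still has about 75% power.

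The cost is wording in Table 1 and the sample-size paragraph, and a less favourable stated power at the lower end. If the per-team range is the figure that changes, the three places that state it need the same edit, and recruitment at each site is affected.

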### Data collection

Data will be collected for each case from interviews and site documentation. Activity logs will also be generated, to capture time spent by all parties, and additional work generated beyond the Needs Rounds meeting. Environmental/contextual data will draw from conceptual work by Estabrook *et al*^39^ and i-PARIHS^34 38^ and be qualitative in nature to dynamically explore each care home’s culture. Interview topics will cover, for example, provider and funding types, leadership, culture, including attitudes towards residents and whether staff feel supported and valued, time/space, staff/resident turnover, introduction of new policies/procedures, and prioritisation of the intervention in workload.

Needs Rounds discussions will be audio-recorded. This will allow analysis of adaptations made by clinical teams for their local areas, alongside the breadth/depth/content of case-based education provided.

Staff capability of adopting a palliative approach (CAPA) will be assessed on a nine-item validated self-report questionnaire.^40^ CAPA has a unidimensional scale; higher scores indicate greater capacity. Internal consistency reliability is very high with a Cronbach’s alpha of 0.95, and split-half-reliability coefficient of 0.93.^40^ Self-complete measures will be taken at baseline from all nursing assistants/care assistants and RNs, and prospectively each month with staff attending Needs Rounds. Final assessment will be taken from all NAs and RNs following the 12-month trial period.

The Quality of Death and Dying Index^41^ (QODDI) will be completed by care home staff for each decedent resident prospectively during implementation. This 17-item questionnaire examines four domains: symptom control, preparation, connectedness and transcendence, on a 0–10 scale, where higher scores indicate a better experience. The Cronbach’s alpha for the QODDI total score is 0.89. Following correspondence with the scale’s originator confirming psychometric robustness of excluding items, one item on access to euthanasia will be removed, as this is not legal in the UK. The QODDI was designed for completion by relatives; however, staff are more likely to have seen the resident in the weeks prior to death so staff completion will result in more reliable and valid data.

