Family perceptions of care will be captured from relatives of residents who are discussed at Needs Rounds, using the CANHELP lite.^42^ Twenty-two items from the second half of the questionniare will be used to collect family self-reported data of satisfaction with care. The Cronbach’s alpha for the total score is 0.88–0.94. A family will only be asked once to complete this measure, even if the resident is discussed at Needs Rounds more than once.

Resident data collection will focus on demographic information and health service use (table 2). Data will be collected from the care homes by care home staff. Training will be provided to ensure robust data collection and reporting. This will be summary level data to ensure anonymity.

**Table 2 T2:** Resident data collection

Type	Variables
Demographic information	Age Ethnicity First language Charlson Comorbidity Index
Deaths	Number of deaths Preferred place of death Actual place of death
Health service use	Clinical role seen in primary care Hospital admissions: Name of hospital Duration of admission Specialty/ward Mode of transport to hospital
Assessments and interventions triggered by Needs Rounds	Physical assessments Clinical investigations, for example, blood/urine tests Referrals to other NHS services Changes in medicines Syringe drivers

Economic evaluation will be based on the intervention and health service cost elements identified in tables 3 and 4. The costs of hospitalisation will be constructed from resident-level data on length of stay collected by the care homes, and costed using the National Tariffs and hospital specific Patient Level Information and Costing System data for both England and Scotland. Total costs for the each of the pre and post periods will be calculated by summing these costs across all residents admitted to hospital from a given site; the benefit is the difference between prehealth and posthealth service-use costs.

**Table 3 T3:** Intervention cost elements

Cost type	Cost detail	Measurement of costs
Direct costs	Intervention costs on-site: Staff time Travel Consumables and equipment Workshop costs	Included within the project budget and therefore directly recorded. Where appropriate additional detail will be collected directly from the care homes.
	Additional NHS staff time attending care home Additional prescriptions	Estimated in the SoECAT, with additional costs recorded by intervention staff as required.

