### Ethics and dissemination

Ethical approval has been granted by the Frenchay REC (287 447) for the implementation study. Separate approval will be sought for the care home survey in 2022.

Participants (table 1) will be provided with a participant information sheet (PIS), including an easy read version for residents. Informed consent will be taken for participation in interviews, questionnaires and Needs Rounds recordings. Care home staff will assess resident capacity and only those who are able to provide informed consent will be included in interviews. Informed consent will not be required for resident data as this will be summary data to ensure anonymity.

Given the sensitive nature of the research, participants may experience distress, particularly residents and relatives. However, the PIS clearly outlines the nature and scope of the study; therefore all participants will be aware of the themes likely to be discussed. Furthermore, the topic guide and questionnaires have been examined by our PPI representatives for appropriateness.

The findings will be disseminated to policy-makers, care home/palliative care practitioners, care home residents/relatives and academic audiences. Infographics, blogs, policy briefings and talks at carer groups/conferences will all be used. An implementation package will be developed for practitioners that provides all the tools and resources required to adopt UK Needs Rounds. The data will be deposited in the open access repository ‘DataSTORRE’.

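### Table 1 makes ability to consent an inclusion criterion for residents discussed at Needs Rounds, which fits neither the triage rule nor the consent rules in the ethics section

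*Protocol article*

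**What the plan says.** The section Target sites and population introduces Table 1 as the inclusion criteria for each participant group. The row for residents discussed at Needs Rounds in phase 2 carries an estimate of n=1500 and ends with "Not engaged in any current safeguarding investigations Able to provide their own informed consent". Interviewees, who may include residents, have a separate row (n=40) with its own capacity criterion. Relatives (n=300) qualify through a resident who was discussed. The care homes row describes Needs Rounds as the homes' new standard of care.

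The Intervention description says that the meetings are "focused on 8–10 residents in each care home who are at risk of dying without a plan in place", with a checklist used to pick the residents. On attendance it says: "Needs Rounds are chaired by a palliative care specialist and attended by care home staff".

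Ethics and dissemination has three relevant statements:
- On consent: "Informed consent will be taken for participation in interviews, questionnaires and Needs Rounds recordings".
- On capacity, after saying that care home staff assess it: "only those who are able to provide informed consent will be included in interviews".
- On data: "Informed consent will not be required for resident data as this will be summary data to ensure anonymity".

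Data collection agrees on the level of the resident data ("This will be summary level data to ensure anonymity") and adds that "Needs Rounds discussions will be audio-recorded".

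**The concern.** A site that follows Table 1 would check whether a resident can consent before putting that resident forward for a Needs Round, or before counting them in the resident data. A site that follows the Intervention description and the ethics section would do neither. The ethics section itself points to Table 1 when it refers to participants, so the two will be read together.

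If Table 1 is followed as labelled, residents without capacity are kept out of something their home has adopted as standard care. Their relatives also lose the only route into the CANHELP sample. If the row is taken instead to define the data sample, these residents drop out of Table 2, including the assessments and interventions triggered by Needs Rounds. Either way the study learns less about a group selected out by criterion, while its primary outcome asks what works, for whom and in what circumstances.

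**Working it through.** The point rests on comparing texts. There is no stated figure to reproduce. The check takes each activity the criterion could govern and asks what the rest of the article says about it.

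1. **Interviews.** Capacity is required, and the ethics section says so. Resident interviewees are already covered by the stakeholder row of Table 1, which has its own capacity criterion. The discussed-residents row is therefore not needed to state the interview rule.

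2. **Summary resident data (Table 2).** The ethics section requires no consent, and Data collection confirms summary level. If the row defines this sample, it conflicts directly with the ethics section. Reading the wording as ability to consent, rather than consent actually given, does not help: residents would still be excluded for lacking an ability that their data do not call for.

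3. **Being discussed at a Needs Round.** This is what the row label says. The Intervention description selects by risk of dying without a plan, using a checklist, and states no capacity condition. The row adds one.

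4. **Recording of the discussions.** The ethics section takes consent for recordings but does not say whose. The Intervention description names the specialist and care home staff as those taking part. Consent for recordings could be where the criterion came from. Even so, the row attaches it to being discussed, not to being recorded.

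On readings 2 and 3 the row disagrees with another section, on reading 1 it is redundant, and on reading 4 it sits in the wrong place.

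**What is and is not reached**

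| Item | Population stated in the article | Reached by the criterion? |
|---|---|---|
| Hospitalisations (Economic analysis) | All care home residents | Not directly |
| 30-home calculation | Homes, rate per bed | Not directly |
| QODDI | Each resident who dies | Not directly |
| CANHELP | Relatives of discussed residents | Yes, if the row governs discussion |
| Table 2 resident data | Not tied to capacity in the ethics section | Yes, if the row governs data |

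**Size.** The article gives no share of residents with capacity, so the loss cannot be estimated. As a side check on the 1500, 30 homes × 52 beds = 1560 beds. The estimate is close to the whole bed stock, which is consistent with no reduction for capacity but does not prove it.

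**The case against.** The strongest counter-argument is that the two sections can coexist. Meetings are recorded, consent is taken for recordings, and participants in Table 1 receive an information sheet, with an easy-read version for residents. A rule that residents whose discussion is recorded must be able to consent is compatible with a waiver for anonymous summary data. The approved ethics documents are not shown and may contain such a rule. This part stands: the contradiction is direct only if the row governs data or discussion, and a reviewer cannot rule out a recording requirement. It does not rescue the row as worded, because the row is labelled by discussion.

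It can also be said that no site would deny a clinical triage meeting to a resident without capacity when the intervention is described as it is. That may prove true in practice, but it relies on sites setting aside a listed inclusion criterion.

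A reader might infer three stronger conclusions, and the article supports none of them:
- *The pool of relatives shrinks, so 300 CANHELP returns need a much higher response.* If the row governs only data, residents without capacity are still discussed and their relatives still qualify, so the figure stays at 300/1500 = 20%. If it governs discussion, other residents can fill the places and the number discussed need not fall. What changes is which families are represented.
- *The hospitalisation comparison is biased or loses power.* It counts all residents of the homes, and the sample size is set in homes.
- *QODDI loses residents without capacity.* It is planned for every resident who dies, with no condition on capacity or on having been discussed.

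**Conclusion.** The point holds as an inconsistency in eligibility and consent. Table 1 attaches ability to consent to being discussed at Needs Rounds. The Intervention description sets no such condition, and the ethics section neither requires consent for resident data nor applies residents' capacity beyond interviews. Followed literally, the row excludes residents without capacity from discussion, and their relatives from CANHELP, or else excludes those residents from the Table 2 data.

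The mismatch in wording is certain. Its consequences depend on which activity the row was meant to govern and on how sites apply it. No magnitude can be given without a capacity rate. The effect falls on who receives and is described under Needs Rounds, and hence on the for-whom part of the primary outcome, rather than on the quantitative hospitalisation result. It should be corrected because a rule that is wrong as written could withhold care or drop residents from the data, and the correction is small.

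**What to change.** - Remove the ability-to-consent criterion from the discussed-residents row of Table 1. Leave the safeguarding criterion as the sponsor's choice.
- Add a sentence saying that neither discussion at a Needs Round nor inclusion in the summary resident data depends on the resident's capacity.
- In Ethics and dissemination, keep consent for interviews, questionnaires and recordings, and state whose consent the recordings need. If the approved ethics documents require the resident's consent, tie the criterion to recording that resident's discussion only, so that a resident who cannot consent is still discussed and counted.

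The text change is one criterion removed and one or two sentences added, with no extra participants or data. The cost lies in checking the approved ethics documents. If they carry the Table 1 wording, an amendment may be needed, because approved eligibility would change. If they already match the ethics section, only the article's table needs correcting.
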